**3.2 Primary Objective**

The primary objective is to determine the feasibility and accessibility of using a video-based PFMT for patients with pelvic floor dysfunction.

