**Confidentiality Statement:**

## Synopsis

|                                                                                                                                                                                                                                                                                                                                                                                      |
|--------------------------------------------------------------------------------------------------------------------------------------------------------------------------------------------------------------------------------------------------------------------------------------------------------------------------------------------------------------------------------------|
| Purpose
The goal of the proposed study is to evaluate the feasibility and accessibility of pragmatic, remote, video-based pelvic floor muscle therapy (PFMT) for patients.                                                                                                                                                                                                 |
| Primary Objective
The primary objective of this study is to determine the feasibility of use of a video-based PFMT.                                                                                                                                                                                                                                                        |
| Secondary Objective
The secondary objective is to determine whether PFMT can improve quality of life (QoL) and reduce symptom burden.                                                                                                                                                                                                                                      |
| Study Design
Patients will complete a series of surveys before and after the intervention. They will complete 8 weeks of video-based PFMT with an initial and final in-person session with a pelvic floor therapist.                                                                                                                                                       |

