# 1 Background/Literature Review

## 1.1 Background

Pelvic floor rehabilitation (PFR) is a group of therapeutic techniques used to help patients with pelvic floor dysfunction, such as urinary incontinence or fecal incontinence. The exercises commonly use in PFR include pelvic floor muscle therapy (PFMT) with biofeedback training, rectal balloon training or electrical stimulation. Together, these techniques aim to improve the strength, tone and endurance of the pelvic floor musculature and sphincter complex. For fecal incontinence, they have shown to decrease symptoms ranging between 50-80%. A meta-analysis looking at 18 trials utilizing PFMT for urinary incontinence found an improvement in symptoms in all studies.

Despite PFMT being shown to be efficacious for numerous different pelvic floor dysfunction disorders, less than 50% of patients referred are compliant with the recommend duration of treatment. Previous studies found that inconvenience, cost, lack of knowledge and discomfort around the concept of PFMT are all reasons why patients may have poor compliance. Patients have shown a positive reception to telehealth-based PFMT visits. It is not known if a hybrid approach to PFMT including both in-person and video-based training videos may help to alleviate some of these barriers while providing the same adequate amount of guidance, improvement in symptoms and QoL for patients. Thus, the purpose of this study is to evaluate the feasibility and acceptability of a web-accessible 8-week video-based PFMT for pelvic floor disorders.

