## 1.2 Prior Experience (if applicable)

Our group conducted a study on patient reported barriers to completion of in-person PFR. We found the average time between referral and attendance of the first PFR session was 10 weeks. The two major barriers to completion included delay in available sessions (24%) and travel distance for attendance (20%). Furthermore, 35% of patients stated they would be amenable to a hybrid option using either telehealth or video-based strategies and 58% of patients would attend more sessions if there was a video-based option.

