### 4.3.2 Eligibility Criteria/Vulnerable Populations

Eligibility will be assessed by a member of the study team reviewing outpatient clinic visits to colorectal surgery and urogynecology clinics at Yale New Haven Hospital and its associated ancillary clinic sites.

In order to be eligible for inclusion in this study, an individual must meet all of the following criteria:

1. Diagnosis of one of the five following diagnoses with referral for PFR
  - a. Urinary incontinence
  - b. Pelvic pain
  - c. Fecal incontinence
  - d. Postpartum-related symptoms
  - e. Constipation
2. 18 years or older
3. English-speaking
4. Access to internet

Vulnerable populations: none

Exclusion criteria:

1. Unable to access web-based videos
2. Unable to speak English

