### **5.3.1 Screening (if applicable)**

Not applicable

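### Accessibility is a stated primary aim, but no outcome measures it, and eligibility plus the 75% video rule remove the patients who would show a lack of access

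*Protocol*

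**What the plan says.** The protocol states its aim in four places, and they do not agree.

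- Synopsis, Purpose: "evaluate the feasibility and accessibility of pragmatic, remote, video-based pelvic floor muscle therapy (PFMT) for patients".
- Synopsis, Primary Objective: "The primary objective of this study is to determine the feasibility of use of a video-based PFMT". Accessibility is not named.
- Section 1.1: "evaluate the feasibility and acceptability of a web-accessible 8-week video-based PFMT for pelvic floor disorders". This is acceptability, a different construct.
- Section 3.2, as the primary objective: to "determine the feasibility and accessibility of using a video-based PFMT for patients with pelvic floor dysfunction".

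Section 4.3.2 makes internet access an inclusion criterion and lists "Unable to access web-based videos" as an exclusion. English is also required. The same section has a study team member review outpatient clinic visits for eligibility, and section 5.3.2 describes reviewing clinic patients with the provider. Section 5.3.1, Screening, reads "Not applicable".

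The primary outcomes in section 4.2.1 are the SUS, the percentage of videos completed, the change in the therapist's graded evaluation, and adverse events. Section 5.4.3 analyses the percentage who learned the therapy, adverse events, usability and graded exercise ability. Section 5.4.6 excludes from the study patients who complete under 75% of the videos or do not attend both therapist visits. Planned enrolment is 10 to 20.

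**The concern.** The population named in section 3.2 is patients with pelvic floor dysfunction, not patients already known to be able to open the website. How accessible a web programme is to that population depends on how many of them can get to it, and the eligibility rule removes those who cannot. The 75% rule acts again after enrolment: it removes patients who lose access or do not use it.

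The rationale makes this more than a matter of wording. Sections 1.2 and 2.1 justify the study by barriers to attending in person, and sections 2.2 and 2.3.2 foresee offering the videos as an alternative treatment. A report that the programme proved accessible would bear directly on that step. Under the plan as written, such a statement would come from the selection rules and not from data.

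**Working it through.** The protocol states no accessibility rate, target or precision, so there is no figure to reproduce. The check compares the objective with the selection rules and then uses simple proportions.

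**Step 1. Access at entry among enrolled patients.** Inputs: n = 10 to 20 (section 4.3.1); every enrolled patient must have access (section 4.3.2).

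Access at entry = n/n = 10/10 or 20/20 = 100%.

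The exact two-sided 95% lower limit for n/n is 0.025^(1/n):

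- n = 10: 0.025^(1/10) = 0.692, interval 69% to 100%.
- n = 20: 0.025^(1/20) = 0.832, interval 83% to 100%.

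These intervals carry no information about access. The numerator equals the denominator by rule, so sampling could not have produced another result.

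**Step 2. Access among otherwise-eligible referrals.** Let s be the share of otherwise-eligible referrals turned away for lack of access. The protocol gives no value, so s is an assumption shown over a range. Access among these referrals = 1 − s. If lack of access were the only reason for not enrolling, the number assessed to enrol n would be n/(1 − s), rounded up.

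| Assumed s | Access among enrolled at entry | Access among otherwise-eligible referrals | Assessed to enrol 10 | Assessed to enrol 20 |
|---|---|---|---|---|
| 0% | 100% | 100% | 10 | 20 |
| 10% | 100% | 90% | 12 | 23 |
| 20% | 100% | 80% | 13 | 25 |
| 30% | 100% | 70% | 15 | 29 |
| 40% | 100% | 60% | 17 | 34 |

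The second column never moves, so data from enrolled patients cannot distinguish between these rows.

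**Step 3. The 75% rule.** Let f be the share of enrolled patients who complete under 75% of the videos, again an assumption. With 20 enrolled and no other losses, the number kept is 20(1 − f):

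- f = 10%: 18 kept.
- f = 25%: 15 kept.
- f = 50%: 10 kept.

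The share of enrolled patients reaching 75% is 90%, 75% and 50% respectively. Among those kept it is 100% each time, and the completion outcome can only take values from 75% to 100%.

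**Step 4. Whether another outcome fills the gap.** The SUS rates ease of use among people who reached the site. Video completion measures adherence and, after section 5.4.6, only its upper range. The graded score measures exercise performance, and adverse events measure safety. None has a denominator that includes patients who could not get in, and none measures uptake among those approached.

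**The case against.** Requiring internet access for a web-delivered programme in a pilot of 10 to 20 is an ordinary choice. The protocol does not define accessibility. Its stated access problem is delay and travel distance, Hypothesis A is about videos that are easy to follow, and the synopsis uses the usability survey for ease of use. The three competing words may simply be loose drafting. Participant-flow accounting is also often left to an analysis plan or the final report.

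Much of this stands, and it rules out several stronger readings.

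- A reader might infer that no screening counts will be kept. The protocol does not say so. Section 5.3.1 has only "Not applicable" under a template heading, while sections 4.3.2 and 5.3.2 describe an eligibility review. The supported statement is that no count is specified.
- A reader might infer that accessibility is 100% by construction in every sense. That holds only for technical access at entry. The SUS is not fixed by eligibility, nor is completion among all enrolled patients. If accessibility was meant as ease of use, the data will say something about it, though only in selected patients.
- A reader might take the section 1.2 finding that "35% of patients stated they would be amenable to a hybrid option" as expected uptake and project how many non-participants go unrecorded. That figure covers telehealth or video and is stated willingness, not trial consent. It gives neither an uptake rate nor an access rate.
- The synopsis primary objective does not name accessibility; only its Purpose line does.

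The central point survives. Section 3.2 names accessibility as primary, the protocol's own outcome list has no measure of it, and two selection rules remove the evidence against it.

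**Conclusion.** The concern holds in this limited form. The study can report feasibility, usability, exercise performance and safety in patients who had access and, under section 5.4.6, completed at least 75% of the videos. It cannot conclude that the programme is accessible to patients with pelvic floor dysfunction, because access at entry reads 100% whatever the rate among referrals.

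The possible gap between that 100% and the true rate is unknown. It is 10 to 40 percentage points if 10% to 40% of otherwise-eligible referrals lack access, but that range is an assumption with no source in the protocol. The conclusion rests on reading accessibility as the ability of referred patients to reach the programme. If another construct was meant, the defect is the inconsistent wording across the synopsis, section 1.1 and section 3.2, which still needs correcting. Either way it should be settled before results are reported. It does not undermine the pilot's other aims.

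**What to change.** Make the synopsis Purpose, the synopsis Primary Objective, section 1.1 and section 3.2 name the same construct, then take one of two routes.

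**(a) Keep accessibility.**

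- Replace the entry in section 5.3.1 with a de-identified tally of pelvic floor rehabilitation referrals reviewed, by reason not enrolled: no internet or cannot access the videos; not English-speaking; declined; other or unknown.
- Add two measures to sections 4.2.1 and 5.4.3, each with its denominator and an exact 95% confidence interval. Access = otherwise-eligible referrals able to use the videos / all otherwise-eligible referrals. Uptake = consented / eligible patients approached.
- Report video completion for all enrolled patients, including those under 75%.

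**(b) If acceptability or feasibility is what is meant**, use that word in the synopsis and section 3.2, and draw no accessibility conclusion.

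Route (b) costs only wording. Route (a) needs no extra patients or visits, but it adds a small recording burden, and the Data Quality Assurance section assigns consent and data extraction to one researcher. A clinic-visit review may not show whether a patient can open the videos, so access status may be unknown for some patients who are not approached. Those patients should be counted and shown as unknown. The tally is best kept as patients are reviewed, since such reasons may not be recoverable from charts later.

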**3.3 Secondary Objective (if applicable)**

To determine whether video-based PFMT can improve symptomatology and QoL.

## 4 Study Design

### 4.1.1 General Design Description

Patients will be enrolled during the clinic visit when they are initially referred for PFR. It will be explained that they are forgoing standard of care of all in-person pelvic floor rehabilitation and will complete the initial survey at this time. They will then have an introductory session with a pelvic floor therapist to assess their baseline function, which does not differ from the standard of care other than the pelvic floor therapist using a graded scoring system to assess exercise completion ability. This initial visit will be prioritized as the waitlist for pelvic floor rehabilitation can be up to 6 months. Then they will complete the 8 weeks of remote, self-directed video-based PFMT. At the midway point after completing 4 weeks of the remote, self-directed video based PFMT, patients will be contacted by a member of the research team to elicit feedback and complete a system usability scale to evaluate patient perspective of the online training program. After this period, they will have another in-person session with the same pelvic floor physical therapist to assess ability to complete exercises successfully with the same graded scoring system. They will then complete a system usability scale survey and repeat the initial surveys for QoL and symptom surveys within 2 weeks of the final in person pelvic floor therapist appointment.

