**Study Schedule**

Patients will be expected to complete a 5–10-minute survey at initial enrollment. They will have one in-person session with a pelvic floor therapist prior to starting the 8-week video-based PFMT course. They will have a midpoint check in after 4 weeks to monitor progress. Afterwards, they will have a final in person session with a pelvic floor therapist along with a final set of surveys that should take an estimated 10-15 minutes. We have also attached a figure with the study design.

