## **5.2 Study Schedule**

Initial surveys completed at initial clinic visit

In person visit standard of care visit with pelvic floor therapist and graded scoring of exercise completion ability (1 hour)

8 weeks of online, video-based PFMT program; videos were created by Yale (website: <https://pelvicfloorthrapy.wixsite.com/yale-video-based-pel>)

Midway check-in with research team and completion of SUS survey (15 minutes)

Completion in person standard of care visit with pelvic floor therapist and graded scoring of exercise completion ability (1 hour)

Completion surveys after 8 weeks of video-based PFMT (within 1 week of in person visit)

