### 5.3.3 Study Visits (is applicable)

1. Initial clinic visit
  - a. SF-12
  - b. And one of the following surveys:
    - i. CCIS
    - ii. PAC-SYM
    - iii. ICIQ-SF
    - iv. POP-SS
2. In person visit with pelvic floor therapist (1 hour)
  - a. Introduction to PFMT clinical visit by a certified pelvic floor therapist
  - b. Graded evaluation of pelvic floor exercises on a scale of 1-3 ( 1= cannot replicate in any meaningful way, 2 = partially, 3 = fully perform)
3. Midway check-in with research team member (15 minutes)
  - a. Elicit feedback on self-direct video-based training
  - b. Completion of SUS
4. Completion in person visit clinical visit with pelvic floor therapist (1 hour)
  - a. Graded evaluation of pelvic floor exercises on a scale of 1-3 (1= cannot replicate in any meaningful way, 2 = partially, 3 = fully perform)
5. Completion survey within 1 week of seeing pelvic floor therapist
  - a. SF-12
  - b. And one of the following surveys:
    - i. CCIS
    - ii. PAC-SYM
    - iii. ICIQ-SF
    - iv. POP-SS
  - c. SUS

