## **6 Trial Administration**

### **6.1 Ethical Considerations: Informed Consent/Assent and HIPAA Authorization**

Consent forms will be Institutional Review Board (IRB)-approved and the participant will be asked to read and review the document online. The consent form will be stored and accessible through RedCap. The trained research assistant will explain the research study to the participant and answer any questions that may arise. This conversation will take place in a private room.

Participants will have the opportunity to carefully review the electronic consent form and ask questions prior to signing. The participants should have the opportunity to discuss the study with their family or surrogates or think about it prior to agreeing to participate. The participant will sign the informed consent document prior to any procedures being done specifically for the study. Participants must be informed that participation is voluntary and that they may withdraw from the study at any time, without prejudice. A physical copy or emailed copy of the informed consent document will be given to the participants for their records. Patients will be compensated with \$25 for each in-person visit with the pelvic floor therapist (initial and final) for a total of \$50. The Informed Consent form is included as an attachment to this protocol.

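### The usability score, a primary outcome, has no assured collection from participants who stop and do not return, and the 75% rule drops any score they gave, so the result describes persisters

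*Protocol*

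**What the plan says.** Protocol Section 4.2.1 lists the SUS among the primary outcomes, and Section 5.4.3 puts the usability score in the primary analysis.

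**Midway SUS.** Section 4.1.1 states: "At the midway point after completing 4 weeks of the remote, self-directed video based PFMT, patients will be contacted", for feedback and a SUS. The Study Schedule in the Synopsis is looser: "They will have a midpoint check in after 4 weeks to monitor progress". Sections 5.1, 5.2 and 5.3.3 list the midway check-in with no condition on progress. The only feedback item in the visit list belongs to this contact: "Elicit feedback on self-direct video-based training".

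**Final SUS.** Section 4.1.1 places it after the closing therapist visit: "They will then complete a system usability scale survey and repeat the initial surveys for QoL and symptom surveys within 2 weeks of the final" in-person appointment. Section 5.3.3 has "Completion survey within 1 week of seeing pelvic floor therapist", and Section 5.2 also gives one week from that visit. Section 5.1 puts the completion surveys after the eight weeks and gives no window.

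**Stopping.** Section 6.1 tells participants that "they may withdraw from the study at any time, without prejudice". No section describes a contact, a SUS or a recorded reason when someone stops the videos or leaves. Section 5.3.2 mentions retention in its title, but its only element of that kind is payment for the two in-person sessions.

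**Analysis.** Section 5.4.6 excludes participants below 75% video completion, or without both therapist visits, and analyses complete cases among the rest.

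**The concern.** The study asks whether patients can use a self-directed video programme. People who find the site hard to follow are plausibly the likeliest to stop. If their scores are not requested, or are requested and then set aside, usability is missing where it is probably lowest and the reported mean is flattering.

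The study's own rationale is non-completion. Section 1.1 says of usual therapy that "less than 50% of patients referred are compliant with the recommend duration of treatment", and Sections 1.2 and 2.1 discuss barriers to completion. A plan that never asks stoppers why they stopped cannot say whether the video format removes those barriers. With 10 to 20 participants, a few missing scores can move the mean.

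This is not something an analysis plan can repair later: a score or a reason that nobody requested cannot be recovered.

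**Working it through.** **No plan figure to reproduce.** The sample of 10 to 20 (Section 5.4.2) rests on analogy with other feasibility studies. The protocol gives no expected SUS, spread or dropout rate. The check is therefore a reading of every scheduled usability contact, followed by an illustration.

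**Step 1: contacts side by side**

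| Protocol place | Midway contact | Final surveys |
|---|---|---|
| Synopsis, Study Schedule | After 4 weeks, no video condition | With the final in-person session |
| 4.1.1 | After 4 completed weeks of videos; SUS and feedback | Within 2 weeks of the closing visit |
| 5.1 | Midway, no condition | After the 8 weeks, no window |
| 5.2 | Midway, SUS, no condition | Within 1 week of the visit |
| 5.3.3 | Midway, SUS and feedback, no condition | Within 1 week of the visit |

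**Step 2: what each kind of participant contributes**

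- *Stops before week 4 and does not return.* No SUS under the strict reading of 4.1.1. A midway SUS is possible under the other sections. No final SUS. Excluded by 5.4.6.
- *Stops in weeks 5 to 6 and does not return.* Midway SUS and feedback, no final SUS. Excluded by 5.4.6, so the midway score is lost.
- *Stops below 75% of videos but attends the closing visit.* Final SUS collected, then excluded by 5.4.6.
- *Reaches 75% and attends both visits.* Kept.

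In no case is a reason for stopping requested. If videos are spread evenly over the programme (assumed), the threshold falls at 0.75 × 8 = 6 weeks.

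**Step 3: possible size.** Let p be the share who persist, M their mean SUS, and g the gap between persisters and stoppers. The all-enrolled mean is pM + (1 − p)(M − g) = M − (1 − p)g. Reporting M overstates it by (1 − p)g. Both p and g are assumed.

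| p | Persisters of 10 / of 20 | g = 10 | g = 20 | g = 30 |
|---|---|---|---|---|
| 0.9 | 9 / 18 | 1 | 2 | 3 |
| 0.7 | 7 / 14 | 3 | 6 | 9 |
| 0.5 | 5 / 10 | 5 | 10 | 15 |

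**Step 4: what the midway score could rescue.** Suppose 20 enrol, 20% stop before week 4, another 20% stop between weeks 4 and 8, and none of them returns (assumed). Then 20 − 4 = 16 give at least a midway SUS under the strict reading, and 20 − 4 − 4 = 12 give the final one. Section 5.4.6 keeps only those 12, so four scores in hand go unused.

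**The case against.** The strongest reply is that the midway contact is in effect a calendar contact. Four other places list it without the completion condition, the research team initiates it, and a contact meant to monitor progress would naturally include people who are behind. This is a fair reading and the protocol permits it. It does not settle the matter, because Section 4.1.1 is the fullest description and says otherwise, and because the generous reading still leaves the final SUS and the reason for stopping uncollected from someone who does not return.

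A reader might infer that everyone who stops early gives no SUS and no feedback. The documents do not support that. A participant who stops after week 4 will normally have given both at the midway contact. Nor does stopping the videos mean missing the closing visit: no section makes attendance depend on viewing, Section 5.4.6 treats the two as separate grounds for exclusion, and each visit is paid. A stopper who attends gives a final SUS.

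A reader might also infer that the study learns nothing from non-completers. That goes too far, since video completion is itself a primary outcome and midway feedback is collected.

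The compliance figure in Section 1.1 concerns referred patients in usual therapy. Session delay and travel, the main barriers reported in Section 1.2, are ones this format is meant to reduce, so 50% stopping is a scenario and not a forecast. The withdrawal wording in Section 6.1 is ordinary consent language; alone, it does not show that those who leave go uncontacted.

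Finally, it can be said that Section 5.4.6 does most of the damage. That stands. It means the exclusion rule and the collection schedule must be changed together, since changing either alone leaves the gap.

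**Conclusion.** The point holds in this form. Where a window is stated for the final SUS, it runs from the closing visit. The midway SUS is conditional on progress in one section and unconditional elsewhere. Nothing is planned for a participant who stops and does not return. Section 5.4.6 then removes non-persisters' scores even where they exist. The primary usability result will describe persisters.

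The direction, too favourable, is probable and not proven: it rests on the assumption that stoppers would score the site lower. The size cannot be known from the protocol. Over the assumed range it runs from 1 point (90% persistence, 10-point gap) to 15 points (50% persistence, 30-point gap). The calculation gives no weight to midway scores from stoppers, which matches Section 5.4.6 as written; counting them would shrink the bias.

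This is a correctable weakness in how a primary outcome is collected and reported. It does not undermine the study as a whole.

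**What to change.** 1. In Sections 4.1.1, 5.2 and 5.3.3, set the SUS at calendar week 4 and week 8 from the start of the video programme, for every enrolled participant, whatever their video progress or visit attendance. Align the Synopsis and Section 5.1. This also removes the one-week versus two-week discrepancy for the final SUS.
2. Use the routes already in place: the survey platform in Section 5.1.1 and the telephone or electronic contact in Section 5.3.2.
3. For participants who stop and still accept contact, add one question on the reason for stopping.
4. Amend Section 5.4.6 so that the SUS is reported for all enrolled participants with any SUS, with the number missing, alongside the 75% completer set. Without this step the added scores would be collected and then excluded.

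The cost is an IRB amendment, one extra question and a few additional contacts among at most 20 people. Some stoppers will not reply, but their number will then be visible.

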## 4.2 Outcome Variables

### 4.2.1 Primary Outcome Variables

SUS, percentage of video completion, change in the graded evaluation of exercises by pelvic floor therapist pre and post intervention, adverse events

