#### 5.1.1 Data Collection

The survey information will be collected by a trained survey either in person or filled out independently by the study participant using a Yale-licensed Qualtrics platform. If there are technical difficulties, a paper-based version of the assessment tool will be substituted and later inputted. This data and the clinical data will be collected from the electronic medical records (e.g., Epic® chart reviews) and will be securely stored in the HIPAA compliant RedCap database. The assessment by the pelvic floor therapist will also be secured inputted into the RedCap database.

At the completion of the study period, we will compare the assessment of PFMT adequacy as assessed by the pelvic floor therapists, usability of the video-based application, and any adverse events as our primary outcome for feasibility and safety. We will analyze the change in the SF-12 score, CCIS, PAC-SYM, pre and post intervention to evaluate any change as our secondary outcome evaluating for efficacy of video-based PFMT.

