### **5.3.2 Recruitment, Enrollment and Retention (if applicable)**

Potential subjects will be identified by reviewing clinic patients with the provider and patients will be targeted for in-person recruitment by the treating provider with the trained research assistant present. We may contact patients of treating providers who have given written agreement to have their patients who are eligible for PFR to be contacted if unable to consent in person. The study will be introduced to the patients by the treating provider and the trained research assistant will consent and complete initial survey administration during the initial visit, or if not able will complete the survey via telephone call or electronic communication. Patients will be compensated a total of \$50 for attendance of the first and last in-person PFMT sessions.

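### The week-4 usability score is collected inside a study-team feedback contact, and survey mode is not held constant, so interviewer and mode effects can enter uncontrolled results

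*Protocol*

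**What the plan says.** Protocol 4.2.1 gives the primary outcomes as "SUS, percentage of video completion, change in the graded evaluation of exercises by pelvic floor therapist pre and post intervention, adverse events". The SUS is collected twice.

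- **Week 4.** Section 4.1.1 says "patients will be contacted by a member of the research team to elicit feedback and complete a system usability scale". Section 5.2 puts the check-in and the SUS in one 15-minute slot. Section 5.3.3 item 3 lists (a) "Elicit feedback on self-direct video-based training" and then (b) the SUS.
- **End of course.** After the final therapist visit, 4.1.1 says "They will then complete a system usability scale survey and repeat the initial surveys for QoL and symptom surveys". In 5.3.3 this SUS is item 5c, with no feedback discussion attached.

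On mode, 5.1.1 allows survey information to be collected "either in person or filled out independently by the study participant using a Yale-licensed Qualtrics platform", with paper as back-up for technical problems. Section 5.3.2 has the trained research assistant administer the initial survey at the first visit. If that is not possible, the patient "will complete the survey via telephone call or electronic communication". No staff contact is described for the completion surveys.

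Section 5.4.1 compares SF-12 and the four symptom scores before and after by paired t-test. The SUS is not on that list. Section 5.4.3 refers to one overall usability score without saying which of the two administrations it means.

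**The concern.** The SUS is a subjective rating, and the first of its two administrations shares a short contact with a conversation about the thing being rated. A patient who has just given an opinion to a member of the study team may rate differently from one who fills in the form alone beforehand. The study has one group, so such an effect has nothing to cancel against and goes directly into the reported score.

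The open choice of mode raises a related problem for the secondary outcomes. As written, the procedures make it plausible that a patient is surveyed by staff at baseline and completes the same instruments alone at the end. The paired difference would then contain a change of mode as well as any change in symptoms or quality of life.

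The protocol recognises the principle elsewhere: 6.4 uses a single therapist to remove inter-rater variability from the exercise grading. For the patient-completed instruments it relies only on their being validated.

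**Working it through.** There is no planned figure to reproduce. The sample of 10-20 is set by precedent (5.4.2), and the protocol gives no SUS threshold, standard deviation or test. The check is therefore of the text, followed by the algebra of how an effect would carry through.

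**1. What is fixed and what is open**

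| Survey occasion | Instruments | Staff contact described | Mode fixed? |
|---|---|---|---|
| Initial visit (5.3.2, 5.3.3 item 1) | SF-12, one symptom survey | Research assistant; telephone or electronic fallback | No |
| Week 4 (4.1.1, 5.2, 5.3.3 item 3) | SUS | Research team member, also eliciting feedback | No |
| Completion (4.1.1, 5.3.3 item 5) | SF-12, one symptom survey, SUS | None | No |

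Nothing requires the SUS to come before feedback, makes self-completion the default, keeps a patient in one mode, or asks for the mode to be recorded.

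**2. Effect on a single SUS score**

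Let *p* be the share of patients whose SUS is staff-administered and *d* the shift that this causes. Then

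reported mean = true mean + *p* × *d*.

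Neither *p* nor *d* is in the documents. As an illustration only, assume *p* = 0.5 and *d* = 5 to 10 points: 0.5 × 5 = 2.5 and 0.5 × 10 = 5 points. Letting *p* run from 0 to 1 with the same *d* gives 0 to 10 points. An effect of discussing the videos first would apply to every patient handled in that order, so it would enter in full for them. Courtesy would push the score up. Talking through difficulties could push it down.

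**3. Effect on a paired change**

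Let *e* be the shift in a given score from staff administration, relative to self-completion. If the mode is the same before and after, *e* cancels within the patient. If a patient goes from staff-administered to self-completed, the observed change is the true change minus *e*. With a share *q* of patients switching this way, the mean change shifts by −*q* × *e*.

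- SF-12, all patients: one switch among 10 shifts the mean by *e*/10 = 0.10*e*; among 20, by *e*/20 = 0.05*e*.
- Symptom surveys, one of four per patient (4.2.2): an even split, which is an assumption, gives 10/4 = 2.5 to 20/4 = 5 patients per survey. One switch among 5 shifts the mean by 0.20*e*; at 2.5 patients the ratio is 0.40*e*.
- If everyone switches, the shift is the full *e* at any sample size.

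The size of *e*, its sign, and whether it favours the videos all depend on the instrument and are unknown here.

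**4. Where each effect reaches a result**

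The SUS is outside the paired-test list, so no planned SUS comparison is exposed to a mode switch. The week-4 effect reaches the primary result only if the week-4 score is the overall usability score in 5.4.3, or is pooled into it. The protocol leaves that open.

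**The case against.** The strongest reply is that the protocol says nothing false here. It leaves survey logistics flexible, as small studies often do, and every safeguard could be applied in practice without breaching it. Research-assistant administration at baseline could mean handing over the Qualtrics form. No decision rule depends on the SUS. Compulsory self-completion could also lose returns in a sample of 10-20. All of this is fair, and it limits the point to an improvement in stated procedures.

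Several stronger readings are tempting, and the documents do not support them:

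- **That modes do differ between time points.** Mode is left open, so it may differ or may be identical throughout.
- **That the week-4 SUS is taken live, after the feedback talk.** This is a reasonable guess for a 15-minute check-in, but no channel is stated, and the order of a list does not fix the order of administration.
- **That patients rate the videos to the people who made them.** Section 5.2 says only "videos were created by Yale". Nothing says that the person making contact produced them, or that difficulties are resolved at the check-in.
- **That lack of blinding is the defect.** With one group there is no allocation to conceal. The issue is interviewer influence and social desirability.
- **That week 4 is the only usability measurement, or that the SUS is the only primary outcome resting on patient report.** The SUS is repeated at the end, and adverse-event capture also relies on patients contacting the investigator (5.1.2).

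What remains is that neither order nor mode is fixed, mode is not recorded, and the primary usability time point is not named.

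**Conclusion.** The point holds as a low-severity, low-cost improvement. One of two administrations of a subjective primary outcome is tied to a study-team feedback contact with no rule that the rating comes first. Survey mode may vary between patients and within a patient across the pre and post surveys. In an uncontrolled design neither effect is removed by comparison.

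The size cannot be derived from the documents. The 2.5 to 5 SUS points shown above rest entirely on an assumed half share of staff administration and an assumed 5 to 10 point effect, and should not be quoted as an estimate of bias. The conclusion assumes only that ratings can depend on how and when they are collected. If the end-of-course SUS is the primary score, the feedback-order part largely falls away and the mode part remains.

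**What to change.** - **5.3.3 item 3:** swap (a) and (b), and state that the SUS is completed before feedback is elicited.
- **5.1.1, with 5.3.2 brought into line:** make self-completion on the existing Qualtrics form the default for SUS, SF-12 and the symptom survey, with paper as back-up. Allow staff administration only for a patient who cannot self-complete. Keep each patient in the same mode at every time point, and record the mode.
- **5.4.3:** name the end-of-course SUS as the primary usability score, and report the week-4 score alongside it.

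The platform and contacts already exist, and no clinical procedure changes. The cost is an approved IRB amendment (6.10), some reminders, and possibly a few more unreturned forms. The self-completion default is the most debatable part, because lost returns matter in so small a sample. If the team prefers not to adopt it, taking the SUS first, holding the mode constant within each patient and recording it would still deal with most of the problem.
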